### Follow up of patients

Patients will be followed for two years. In addition, at the 2-year follow-up (FU) visit, any secondary intervention planned will be recorded. A schedule of events is shown in Figure 4.

**Figure 4 F4:**
[figure not shown]
**Schedule of follow-up measurements**.

Clinical assessments will occur at the time of admission to the hospital (baseline), one week (3-10 days window), three weeks (11-28 days window), six weeks (4-8 weeks window), three months weeks (11-15 weeks window), six months (5-7 months window), 12 months (11-13 months window), and 24 months (24-26 months window) after surgery (HA group) or after start of conservative treatment (conservative group).

At baseline, multiple intrinsic (i.e., patient-related) and injury-related variables will be collected. At the three, six, 12, and 24 months FU visit, an independent researcher will determine the Constant score. In order to prevent bias the Constant score will be determined by an independent assessor. At each clinic FU visit, the researcher will ascertain patient status (i.e., secondary interventions, adverse events/complications, deaths), and will verify information within medical records. At each visit, patients will be asked to complete the questionnaires relating to disability (DASH score), and VAS for pain. From six weeks onwards, SF-36, EQ-5D, and health care consumption questionnaires will also be completed. A postal version of the latter questionnaire will be sent at 18 months in order to minimize recall bias.

As part of standard of care, X-rays of the shoulder will be made at the time of admission to hospital (baseline), at one, three and six weeks, and three and 12 months after surgery (HA group) or start of conservative treatment. CT scans that will be conducted pre-treatment, which are required for correct classification of the fracture, are also part of standard of care. As part of this trial, one additional CT-scan will be made at 12 months FU in order to determine consolidation (i.e. vanishing tubercles).

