**Figure 2 F2:**
[figure not shown]
**Head-split components**. Classic head-split geometry (left) and special head-split geometry where both fragments remain perfused (right). Categories eligible for enrolment into the current trial are indicated in red boxes. **Reprinted from J Shoulder Elbow Surg, 13, Hertel R, Hempfing A, Stiehler M, Leunig M: Predictors of humeral head ischemia after intracapsular fracture of the proximal humerus, pp 427-433, with permission from Elsevier**.

4. Operative treatment within 21 days (if randomized for HA)

5. Provision of informed consent by patient

6. Assurance that the surgeon who will perform HA has attended the pre-trial HA course (Erasmus MC Skills lab)

If any of the following criteria applies, patients will be excluded:

1. Polytrauma patients

2. Patients with an additional traumatic injury of the affected arm

3. Patients with a pathological, recurrent or open humerus fracture

4. Patients with an impaired shoulder function (i.e., stiff or painful shoulder, neurologic disorder of the upper limb, or diagnosed rotator cuff impairment) prior to the injury

5. Retained hardware around the affected humerus

6. Patients with a disorder of bone metabolism other than osteoporosis (e.g., Paget's disease, renal osteodystrophy, osteomalacia)

7. Moderate or severe cognitively impaired patients (i.e., Mini-Mental Status Examination (MMSE) Six Item Screener with 3 or more errors)

8. Likely problems, in the judgment of the investigators, with maintaining follow-up (e.g., patients with no fixed address will be excluded)

9. Insufficient comprehension of the Dutch language to understand a rehabilitation program and other treatment information in the judgment of the attending physician

The Six Item Screener for dementia (exclusion criterion 7) is a brief and reliable instrument for identifying subjects with cognitive impairment. The patient is asked to remember three words (e.g., apple, table, penny), then to say the day of the week, month, year, and finally to recall the three words without prompts. Using a cut-off of 3 or more errors, the sensitivity and specificity of the Six Item Screener for diagnozing dementia was 88.7 and 88.0, respectively [20].

Exclusion of a patient because of enrolment in another ongoing drug or surgical intervention trial will be left to the discretion of the attending surgeon, on a case-by-case basis.

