**Figure 3 F3:**
[figure not shown]
**Examples of proximal humerus fracture, managed by endoprosthesis (A) or conservative treatment (B)**.

In order to ensure similar peri-operative regimens, participating centers will standardize the following key aspects of pre-and post-operative care. Pre-operatively, patients will receive antibiotic prophylaxis (single dose) and thromboprophylaxis, and their condition prior to surgery will be optimized if necessary. Post-operatively, patients will receive thomboprophylaxis during hospital stay (e.g., unfractionated heparin, Low Molecular Weight Heparin (LMWH), or equivalent). Surgical delay and physical therapy and rehabilitation programs be recorded but not standardized.

Conservative treatment (Figure 3B) is defined by treatment with a collar and cuff for three weeks. After one week circumduction exercises will start under supervision of a physical therapist. At three weeks after trauma, full range of motion excercises will be initiated if tolerated. Physical therapy sessions will be held at regular intervals, preferably two times a week during 12 weeks. The exact frequency and duration of physical therapy will largely depend upon the extent of functional recovery. This will be left at the discretion of the therapist. Details of the therapy program will be recorded.

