a) Intrinsic variables (baseline data): dominant side, age, gender, American Society of Anesthesiologists (ASA) grade, alcohol and tobacco consumption, comorbidity including osteoporosis, household composition, and medication use

b) Injury related variables: affected side, mechanism of injury, fracture classification (Hertel)

c) Intervention-related variables: surgical delay (i.e., time between fracture and surgery; HA-group only), time between injury and start of physical therapy, days of collar and cuff use, and total number of physical therapy sessions

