### Statistical analysis

The research data will be reported following the CONsolidated Standards of Reporting Trial (CONSORT). Data will be analyzed using the Statistical Package for the Social Sciences (SPSS) version 16.0 or higher (SPSS, Chicago, Ill., USA). Normality of continuous data will be tested with the Shapiro Wilk test, and homogeneity of variances will be tested using the Levene's test. Protocol violations will be recorded; data will be analyzed with and without patients with protocol violation.

Differences in baseline characteristics (i.e., intrinsic and injury-related variables) between both intervention groups will be assessed using the Student's T-test (parametric numeric data), Mann-Whitney U-test (non-parametric numeric data) or Chi-square test (categorical data). Data will be presented as mean ± SD (parametric data) or medians and percentiles (non-parametric data).

Univariate analysis will be performed to test the difference in primary and secondary outcome measures between the intervention groups using the Student's T-test (parametric data), Mann Whitney U-test (non-parametric data) or Chi-square analysis (categorical data).

Multinomial logistic regression analysis will be performed to model the relation between different covariates and the Constant score. Intrinsic and fracture-related variables that display a p-value < 0.5 in univariate analyses will be added as covariate. Similar models will be made to model the relation between covariates and the other outcome measures.

A p-value < 0.05 (2-sided tests) will be taken as threshold of statistical significance.

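### Visits are timed from surgery in the HA arm but from start of treatment in controls, so the same early visit label can mean up to about 21 more days since injury in the HA arm

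*Protocol article*

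**What the plan says.** All references are to the protocol article.

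- **Visit clock** (Follow up of patients): assessments are timed "after surgery (HA group) or after start of conservative treatment (conservative group").
- **Early windows** (same section): "one week (3-10 days window), three weeks (11-28 days window), six weeks (4-8 weeks window").
- **Time to surgery** (Study population, inclusion criterion 4): "Operative treatment within 21 days (if randomized for HA"). The starting point of the 21 days is not given.
- **Control over delay** (Interventions): "Surgical delay and physical therapy and rehabilitation programs be recorded but not standardized".
- **Outcomes at each visit** (Follow up of patients): "At each visit, patients will be asked to complete the questionnaires relating to disability (DASH score), and VAS for pain". The Constant score is taken at 3, 6, 12 and 24 months.
- **Analysis** (Statistical analysis): "Univariate analysis will be performed to test the difference in primary and secondary outcome measures between the intervention groups". Model covariates come from the intrinsic and fracture-related variables.
- **Recorded data** (Outcome measures): surgical delay, defined from fracture to surgery and for the HA arm only, is listed with the intervention-related variables. So is "time between injury and start of physical therapy", which is not limited to one arm.

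**The concern.** The trial compares two treatment strategies by intention to treat. For that comparison both arms should be observed at the same time after a common starting point. Here the HA clock starts only once surgery has been done, while the control clock starts with conservative care. Two features of the text suggest that conservative care begins close to injury: patients are approached in the emergency department, and the control rehabilitation has a milestone at three weeks after the trauma.

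A three-week DASH score can therefore describe patients three weeks from fracture in one arm and up to about six weeks in the other. Because allocation produces the gap, randomisation cannot balance it. The stated analysis does not correct it either: the tests are unadjusted, and surgical delay falls outside the covariate pool. As delay exists in one arm only, adding it as a covariate would not solve the problem.

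Two further consequences follow. No HA visit after baseline covers the wait for surgery. And an HA-allocated patient who is never operated on has no defined visit origin. At stake is how early differences in disability and pain are read.

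**Working it through.** The plan gives no figure for the gap between the clocks, so there is none to reproduce. The sample size is not in question.

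**Inputs.** Windows from Follow up of patients, in days: one week 3–10, three weeks 11–28, six weeks 28–56 (4–8 weeks), three months 77–105 (11–15 weeks), 12 months about 335–396 (11–13 months). Ceiling on surgery: 21 days.

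**Definition.** Let d be the number of days by which surgery falls later after injury than the start of control treatment. At the same label an HA patient is d days further from injury. For a control window from day a to day b, the HA window is a + d to b + d, so

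shared days = max(0, b − (a + d) + 1).

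Example, one week with d = 7: 10 − (3 + 7) + 1 = 1.

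| Visit | Shared days, d = 7 / 14 / 21 | Nominal day, control | Nominal day, HA, d = 7 / 14 / 21 | d ÷ nominal day |
|---|---|---|---|---|
| 1 week | 1 / 0 / 0 of 8 | 7 | 14 / 21 / 28 | 100% / 200% / 300% |
| 3 weeks | 11 / 4 / 0 of 18 | 21 | 28 / 35 / 42 | 33% / 67% / 100% |
| 6 weeks | 22 / 15 / 8 of 29 | 42 | 49 / 56 / 63 | 17% / 33% / 50% |
| 3 months | 22 / 15 / 8 of 29 | 91 | 98 / 105 / 112 | 8% / 15% / 23% |
| 12 months | 55 / 48 / 41 of 62 | 365 | 372 / 379 / 386 | 1.9% / 3.8% / 5.8% |

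**Thresholds.** The one-week windows share no day when 10 − (3 + d) + 1 ≤ 0, that is d ≥ 8. The three-week windows share none when 28 − (11 + d) + 1 ≤ 0, that is d ≥ 18. At d ≤ 7 every pair of windows shares at least one day.

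**Primary outcome.** The nominal 12-month HA visit falls no later than 365 + 21 = 386, inside 335–396.

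**Range of d.** The maximum of 21 assumes that the 21 days run from injury and that control treatment starts on the day of injury. If control treatment starts 3 or 7 days after injury, the maximum is 21 − 3 = 18 or 21 − 7 = 14. If both run from randomisation, it is again 21. If the 21 days ran from randomisation but control treatment dated from injury, d could exceed 21 by the gap between those two dates.

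**Which early day supports a common-origin comparison.** Let r be days from randomisation to surgery, 0 ≤ r ≤ 21. The nominal HA visits fall at 7 + r, 21 + r and 42 + r.

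- Day 42: 21 + r ≤ 42 ≤ 42 + r for every permitted r, so the three- and six-week HA visits always bracket it, and both are post-operative.
- Day 21: the one-week visit precedes it only if 7 + r ≤ 21, that is r ≤ 14.
- Day 7: no nominal HA visit falls on or before it unless r = 0.

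So day 42 is the first of these three days that the present schedule supports for all operated HA patients.

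**The case against.** The strongest reply is that counting from start of treatment is a common and coherent convention. It fits the rehabilitation programmes, which both begin with treatment, and it answers a real question: recovery at equal time after treatment. The article states no one-, three- or six-week hypothesis; its only time-specific hypothesis is the Constant score at one year. How early visits are analysed may properly be left to an analysis plan that is not shown. Twenty-one days is also a ceiling, and the actual delays may be short.

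Much of this stands. The missing detail about early time points is not a fault in the article. What the article does fix is the pair of visit clocks, and the covariate pool it names leaves the gap uncorrected. An early between-arm comparison by visit label inherits the shift.

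A reader might infer that the extra days favour HA. The documents do not support this. They give no recovery curve for DASH or VAS, and an HA patient at the one-week visit is also only 3–10 days past an operation, so the net effect could go either way. A reader might also want to turn the shift into a false-positive rate. That would need a shift in SD units, which nothing in the documents ties to any delay.

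**Conclusion.** The point holds as a minor one. The arms have different time origins, and at the early visits the same label can mean up to about 21 more days since injury in the HA arm. That maximum rests on two readings the article does not state: that the 21 days run from injury, and that control treatment starts at or near injury. The distribution of delay is not given, so the true gap lies anywhere from none to the ceiling, and the size and direction of any bias in early DASH and VAS are unknown.

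A reader might take this as a threat to the main result. It is not one. At 12 months the shift is at most 21/365 = 5.8%, and a nominal visit stays within the stated window.

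**What to change.** 1. Name the date of randomisation as the common time origin for between-arm comparisons in all randomised patients, including HA-allocated patients who are not operated on.
2. Analyse DASH and VAS from six weeks onward by actual days since randomisation, for example with a longitudinal model that estimates the arm difference at day 42.
3. Label the one- and three-week between-arm comparisons as descriptive recovery after treatment.
4. Report days since injury at each visit, by arm.

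The visit schedule can stay as it is, which avoids HA assessments that fall before surgery. Restricting the one- and three-week comparisons to days that both arms cover is not a good alternative. It would keep mainly HA patients with short delays (at one week only those with d of 7 or less), and delay arises after randomisation and may depend on the patient's condition.

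The cost is a short addition to the analysis section, one table and slightly more analysis work, and the trial gives up a formal between-arm test at one and three weeks. The article does not list randomisation and visit dates as data items, but web-based randomisation and dated visit windows mean the trial must hold them.

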**Methods/Design:**

A prospective, multi-center RCT will be conducted in nine centers in the Netherlands and Belgium. Eighty patients over 65 years of age, who have sustained a three-or four part, or split head proximal humeral fracture will be randomized between primary hemiarthroplasty and conservative treatment. The primary outcome is the Constant score, which indicates pain and function. Secondary outcomes include the Disability of the Arm and Shoulder (DASH) score, Visual Analogue Scale (VAS) for pain, radiographic healing, health-related quality of life (Short-form-36, EuroQol-5D) and healthcare consumption. Cost-effectiveness ratios will be determined for both trial arms. Outcome will be monitored at regular intervals over the subsequent 24 months (1, 3 and 6 weeks, and 3, 6, 12, 18, and 24 months). Data will be analyzed on an intention to treat basis, using univariate and multivariable analyses.

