The EuroQol (EQ-5D) is a validated and extensively used general health questionnaire to measure quality of life [27,28]. It is recommended for the assessment of QoL in trauma patients, especially for economic assessments [29,30]. EQ-5D has been developed by the EuroQoL Group in order to provide a simple, generic measure of health for clinical and economic appraisal [31]. EQ-5D consists of the EQ-5D descriptive system and the EQ Visual Analog Scale (EQ VAS). The EQ-5D descriptive system comprises five dimensions: mobility, self-care, usual activities, pain/discomfort, and anxiety/depression. Each dimension is marked as either no problems, some problems, or severe problems, which results in a 1-digit number expressing the level selected for that dimension. The digits for five dimensions are combined in a 5-digit number describing the respondent's health state. The EQ VAS records the respondent's self-rated health on a vertical, visual analog scale. Scores ranging from 0 ('Worst imaginable health state') to 10 ('Best imaginable health state') can be used as a quantitative measure of health outcome as judged by the individual respondents.

Cost measurement will be in accordance with Dutch guidelines for economic evaluations. Healthcare consumption data will be collected using a custom-made questionnaire. Health care costs will include costs of general practice care, medical specialist care, physical therapy, hospitalization, medication, home care, and other costs directly associated with diagnosis, treatment and rehabilitation. Where possible standard cost prices will be used as published by Oostenbrink will be used [32]. In accordance with guidelines for differential discounting, effects will be discounted at a rate of 1.5% and costs at 4% per year [33]. Results will be presented with 95% confidence intervals.

The incremental cost-effectiveness ratio of HA versus conservative treatment will be expressed in a cost-utility ratio, i.e., in terms of cost per Quality-Adjusted Life Years (QALY). Cost-utility ratios will be calculated by dividing the difference in mean costs of the two interventions by the difference in their mean effects. Policy makers and healthcare economists have proposed that costs varying from € 25,000 up to € 75,000 (US$ 31,600 - US$ 94,700) per QALY may be considered as acceptable [34,35].

In addition to the outcome variables mentioned above, the following data will be collected:

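### The text schedules EQ-5D only from six weeks and names no baseline utility, so the early part of the cost-per-QALY result must be assumed

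*Protocol article*

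**What the plan says.** Under Outcome measures, the protocol article states that the economic comparison will be "expressed in a cost-utility ratio, i.e., in terms of cost per Quality-Adjusted Life Years (QALY", and it presents EQ-5D as suited to economic assessment. Under Study objectives, it expects hemiarthroplasty (HA) to be the more cost-effective option despite higher initial costs.

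The collection times are under Follow up of patients:

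- Baseline: "At baseline, multiple intrinsic (i.e., patient-related) and injury-related variables will be collected". The lists of these variables under Outcome measures contain no utility measure.
- Visits generally: "At each visit, patients will be asked to complete the questionnaires relating to disability (DASH score), and VAS for pain".
- Utility, SF-36 and resource use: "From six weeks onwards, SF-36, EQ-5D, and health care consumption questionnaires will also be completed". The visit window is given as "six weeks (4-8 weeks window").
- 18 months: "A postal version of the latter questionnaire will be sent at 18 months in order to minimize recall bias".

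Visits are timed from surgery in the HA arm and from the start of treatment in the conservative arm. The inclusion criteria allow up to 21 days for the operation, and the Interventions section says that surgical delay is recorded but not standardised.

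**The concern.** A QALY total is the area under the utility curve from a common starting point. With the first observation at about six weeks, the first segment of the curve has no data in either arm.

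That segment is not the same for the two arms. By the Interventions section, it contains the operation and a sling for two days to one week in the HA arm, and three weeks in a collar and cuff in the conservative arm. An early utility difference could favour either arm, and giving both arms the same assumed value would hide it.

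Nothing else named in the text supplies the missing values. SF-36 starts at the same time as EQ-5D, and DASH and VAS pain are not utilities. Resource use is evidently asked about past periods, since recall bias is the stated reason for the 18-month mailing. Early costs can therefore still be collected at six weeks, but the article describes no comparable look-back for utility. The ratio could then contain early costs, including the operation, without observed early effects.

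Two further consequences follow. Without a baseline value, the QALY difference cannot be adjusted for chance imbalance in utility in a trial of 80 patients. And because the HA clock starts at surgery, the unmeasured time since injury can be longer in that arm.

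**Working it through.** The article gives no figure for this point, so there is nothing to reproduce. The check sizes the gap.

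**Inputs from the article:** first EQ-5D at 6 weeks (window 4 to 8 weeks); horizon 24 months; surgery within 21 days; acceptable cost of EUR 25,000 to 75,000 per QALY.

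**Assumptions, because the documents give no utilities:** a mean between-arm utility difference d over the gap of 0.05 to 0.30, in either direction; an incremental QALY measured after six weeks, L, of 0.02, 0.05 or 0.10.

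**1. Length of the gap** = weeks / 52.18.

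| First EQ-5D at | Years | Share of 24 months |
|---|---|---|
| 4 weeks | 0.077 | 3.8% |
| 6 weeks | 0.115 | 5.75% |
| 8 weeks | 0.153 | 7.7% |

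**2. Unobserved incremental QALY** = d × 0.115, valued at the article's two thresholds.

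| Assumed d | QALY per patient | At EUR 25,000 | At EUR 75,000 |
|---|---|---|---|
| 0.05 | 0.006 | EUR 144 | EUR 431 |
| 0.10 | 0.012 | EUR 287 | EUR 862 |
| 0.20 | 0.023 | EUR 575 | EUR 1,725 |
| 0.30 | 0.035 | EUR 862 | EUR 2,587 |

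**3. Effect on the cost-utility ratio.** With the cost difference fixed, the ratio including the early part, divided by the ratio omitting it, is L / (L + d × 0.115). Negative d means an early loss with HA.

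- L = 0.10: d = −0.10 gives 0.10/0.0885 = 1.13; d = +0.10 gives 0.10/0.1115 = 0.90; d = −0.30 gives 0.10/0.0655 = 1.53; d = +0.30 gives 0.10/0.1345 = 0.74.
- L = 0.05: d = −0.10 gives 0.05/0.0385 = 1.30; d = +0.10 gives 0.05/0.0615 = 0.81; d = −0.30 gives 0.05/0.0155, about 3.2; d = +0.30 gives 0.05/0.0845 = 0.59.
- L = 0.02: d = −0.30 gives a total of 0.02 − 0.0345 = −0.0145, so the sign reverses.

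**4. Timing by arm.** An HA patient operated on at day 21 and seen six weeks later has the first EQ-5D at 21 + 42 = 63 days, or 63/365 = 0.17 years, after the 21-day clock starts. A conservative patient has it 42 days (0.115 years) after treatment start. The article does not say from which event the 21 days run. If they run from injury and conservative treatment starts promptly, the extra unmeasured time in the HA arm is at most 21 days at the nominal visit time.

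**5. The 18-month point.** With EQ-5D at 12 and 24 months only, a between-arm departure e from a straight line at 18 months gives an error of 0.5 × e. For an assumed e of 0.02 to 0.05, that is 0.010 to 0.025 QALY.

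**The case against.** The strongest reply is that the gap is short, the outcome is secondary, and the amounts are small against sampling error. If the QALY SD is assumed to be 0.15 to 0.30, with 30 to 40 patients per arm, the standard error of the difference runs from 0.15 × √(2/40) = 0.03 to 0.30 × √(2/30) = 0.08. The unobserved 0.006 to 0.035 is then about one standard error or less. This stands as a limit on importance. It does not remove the point, because an error from an assumed early value is not reflected in the confidence interval.

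DASH and VAS pain at 1 and 3 weeks could support arm-specific imputation of early utility. That is fair, so the early period need not be omitted or set equal in both arms. It would still be modelled rather than observed. How QALYs are calculated may properly be left to a fuller plan and is not faulted here; the point concerns the collection times that the text fixes.

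Several stronger readings are tempting but unsupported:

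- A reader might infer that the treatments differ most in the first six weeks. The article shows only that surgery and immobilisation differ then; its own hypothesis places the Constant-score benefit at one year.
- A reader might see a clash with the abstract, which lists "1, 3 and 6 weeks, and 3, 6, 12, 18, and 24 months". That list names no instruments, and a resource-use questionnaire at 18 months is consistent with it. The most natural reading is that only this questionnaire is posted, but months 12 to 24 are bracketed by two EQ-5D values, so this is a minor interpolation matter.
- A reader might quote the gap as up to 0.0345/0.05 = 69% of the QALY gain. That pairs the largest assumed early difference with a small assumed gain.
- A reader might say that baseline imbalance passes straight into the QALY difference. Under randomisation it is chance, and it carries over only as far as baseline and later utility are correlated.
- A reader might assume that DASH and VAS are completed at baseline. The text does not clearly establish this.

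Finally, the follow-up schedule figure was not available, so an earlier EQ-5D listed there cannot be ruled out.

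**Conclusion.** The point holds in limited form. As the text stands, utility is first observed at six weeks, no baseline utility is named, and the cost-per-QALY result depends on assumed values for 5.75% of its horizon (3.8% to 7.7% across the visit window). The arms differ in surgery and immobilisation during that time. The unmeasured period since injury can also be longer in the HA arm.

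The size rests entirely on assumed utilities: about 0.006 to 0.035 QALY per patient, direction unknown. This is of little consequence if the total QALY difference is large. It can move the ratio materially, or reverse its sign, if that difference is a few hundredths of a QALY. The Constant-score comparison is unaffected. The change is worth making because it is cheap and early utilities cannot be observed once a patient has passed these visits.

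**What to change.** - Add EQ-5D at baseline, ideally before the allocation is known, and at the existing 1- and 3-week visits.
- Compute QALYs by area under the curve from randomisation in both arms, using actual assessment dates so that surgical delay counts as observed time.
- Adjust the QALY difference for baseline EQ-5D.
- For patients already past these visits, impute early utility, for example from DASH and VAS pain at 1 and 3 weeks using their relation to EQ-5D at six weeks. Report a sensitivity analysis in which the assumed early difference varies in both directions.
- If the schedule figure lists an earlier EQ-5D, reconcile it with the text under Follow up of patients.
- Optionally, add EQ-5D to the 18-month mailing and state which questionnaires it contains.

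The cost is a short extra form for recently injured patients and a minor amendment. No visits or staff are added. Early values for patients already enrolled will remain modelled.
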